# Magnesium hydroxide versus macrogol/electrolytes in the prevention of opioid-induced constipation in incurable cancer patients: study protocol for an open-label, randomized controlled trial (the OMAMA study)

**DOI:** 10.1186/s12904-023-01143-2

**Published:** 2023-03-14

**Keywords:** Opioids, Constipation, Magnesium hydroxide, Macrogol/electrolytes, Laxative, Cancer, Palliative care, Clinical trial

## Abstract

**Background:**

Opioid-induced constipation (OIC) is a common symptom in cancer patients treated with opioids with a prevalence of up to 59%. International guidelines recommend standard laxatives such as macrogol/electrolytes and magnesium hydroxide to prevent OIC, although evidence from randomized controlled trials is largely lacking. The aim of our study is to compare magnesium hydroxide with macrogol /electrolytes in the prevention of OIC in patients with incurable cancer and to compare side-effects, tolerability and cost-effectiveness.

**Methods:**

Our study is an open-label, randomized, multicenter study to examine if magnesium hydroxide is non-inferior to macrogol/electrolytes in the prevention of OIC. In total, 330 patients with incurable cancer, starting with opioids for pain management, will be randomized to treatment with either macrogol/electrolytes or magnesium hydroxide. The primary outcome measure is the proportion of patients with a score of < 30 on the Bowel Function Index (BFI), measured on day 14.

The Rome IV criteria for constipation, side effects of and satisfaction with laxatives, pain scores, quality of life (using the EQ-5D-5L), daily use of laxatives and escape medication, and cost-effectiveness will also be assessed.

**Discussion:**

In this study we aim to examine if magnesium hydroxide is non-inferior to macrogol/electrolytes in the prevention of OIC. The outcome of our study will contribute to prevention of OIC and scientific evidence of guidelines on (opioid-induced) constipation.

**Trial registration:**

This trial is registered at clinicaltrials.gov: NCT05216328 and in the Dutch trial register: NTR80508. EudraCT number 2022–000408-36.

## Background

Opioid-induced constipation (OIC) is a common symptom in cancer patients treated for pain and occurs in up to 59% [1]. It has a significant negative effect on the quality of life of patients, due to physical problems, psychological problems and social consequences [1–5]. OIC may cause problems that range from daily discomfort with social insecurity and disability to intestinal obstruction. This leads to limitations in self-management and a risk of need for more care, including hospital admission. Constipation is even more burdensome in the palliative phase of cancer, when opioid use is most common due to a high prevalence of pain and other risk factors for constipation [1, 6]. Thus, attention for prevention and early recognition of OIC is needed.

Laxatives are recommended for prevention of OIC, although there is little evidence to support this [7]. One randomized, open-label study compared macrogol/electrolytes with sodium picosulphate and lactulose in ambulatory cancer patients starting with opioids and showed that both macrogol/electrolytes and sodium picosulphate were more effective than lactulose in preventing OIC [8].

Another laxative used for prevention of OIC is magnesium hydroxide, a magnesium compound also used as an antacid. The use of magnesium compounds for constipation dates back to as early as the eighth century [9]. Over the years different kinds of magnesium compounds (e.g. magnesium oxide, magnesium hydroxide, magnesium citrate) have been used [9]. As magnesium oxide is transformed in the stomach to magnesium hydroxide, these drugs are considered to be the same. Nowadays, magnesium hydroxide is the most commonly used magnesium compound in the United States and Europe [9]. There has been only one randomized study about prevention of OIC by a magnesium compound. This recent study compared magnesium oxide with naldemedine (a peripheral μ-receptor antagonist) in preventing OIC. It showed that naldemedine resulted in significantly better constipation-related quality of life, measured with two different questionnaires, better stool consistency and less constipation based on Rome IV criteria, both after two weeks and three months of treatment [10]. There were no statistical differences in number of spontaneous bowel movements per week and in quality of life as measured with the short form-36.

At present, naldemedine is not yet globally available [11] and costs on average 376,74 dollars (348,19 euros) for a 30-day supply [12], making it is less accessible compared to traditional and widely available laxatives such as macrogol/electrolytes or magnesium hydroxide with a cost of around 5 euros (5,40 dollars) for a 30-day supply [13, 14].

Despite the lack of evidence from other randomized controlled trials on the prevention of OIC by the more traditional laxatives, Dutch and other national guidelines on constipation in cancer patients recommend either macrogol/electrolytes or magnesium compounds (including magnesium hydroxide) as first-line laxative treatment to prevent OIC [15–17].

To gain evidence for these guideline recommendations, the OMAMA study examines if magnesium hydroxide is non-inferior to macrogol/electrolytes in the prevention of OIC in patients with metastatic or locally advanced incurable cancer and compares side-effects, tolerability and cost-effectiveness.

## Methods

### Study design

The OMAMA study is an open-label, randomized, multi-center study to examine whether magnesium hydroxide is non-inferior to macrogol/electrolytes in the prevention of OIC. This study will be conducted in eleven hospitals throughout The Netherlands. The trial is designed in accordance with the Declaration of Helsinki and the principles of Good Clinical Practice (GCP) set by the International Conference of Harmonization (ICH) [18, 19]. It has been approved by the Medical research Ethics Committee of Amsterdam UMC. The study is registered in the Dutch Trial Register, identifier 80508; EudraCT number 2022–000408-36. Patient recruitment and data collection have started in October 2022.

### Study population

Both patients from the outpatient clinic and hospitalized patients from eleven academic and non-academic hospitals will be recruited. We will ask patients with metastatic or locally advanced incurable cancer to participate in this study at the moment that they will start to use slow release or transdermal opioids for pain. Additional inclusion criteria are that the patient is ≥ 18 years old and able to complete a Dutch questionnaire. Previous treatment with opioids is allowed, if discontinued for more than four weeks before the start of the study.

Exclusion criteria for participation include patients with contra-indications for laxatives; use of laxatives during the previous four weeks; severely impaired renal function, defined as a serum creatinine > 180 umol/l; and an estimated life expectancy < 3 months.

### Informed consent procedure

Patients will be asked to participate in the study by the physician who prescribes the opioid for pain and will give them a package containing the patient information leaflet (PIL) and the informed consent form. In case of a patient in the outpatient clinic, the patient will be given the time to read the PIL directly after the consult. The local investigator will then give additional information, answer all questions and ask for informed consent. In case of a hospitalized patient, the patient will receive the PIL and informed consent form on the day that opioid use will start. The local investigator will then meet the patient the next day to give additional information, answer all questions and ask for informed consent. When informed consent is given, the PIL is signed twice by the patient and the investigator. After signing informed consent patients are free to withdraw from the trial at any moment.

### Randomization, blinding and treatment allocation

Patients will be randomized after fulfilling eligibility criteria and written informed consent. The randomization will be 1:1 using computerized block randomization with varying block sizes of 2 and 4 in random order. Randomization will be stratified by center and presence of constipation at the start of the study, defined as a score ≥ 30 on the Bowel Function Index (BFI, see paragraph ‘study measurements’). Randomization will be performed by the local researcher after baseline assessments.

### Treatment

Patients will be treated with either macrogol/electrolytes or magnesium hydroxide in a standard dosing regimen. Macrogol/electrolytes is started at a dose of 1 sachet (containing 13,125 g of macrogol) once daily and magnesium hydroxide at a dose of 724 mg t.i.d., both orally. Macrogol/electrolytes is regarded as the standard treatment (usual care) to which magnesium hydroxide will be compared. The dose of macrogol/electrolytes and magnesium hydroxide may be increased to 2 sachets daily or 1448 mg t.i.d., respectively, or may be decreased or discontinued because of intolerance or side effects during the study period. To determine whether a change of the dosage is needed, a contact moment with the local investigator by telephone will take place on day 7.

### Study measurements

Demographic and baseline data will be extracted from the medical record. This includes sex, age, performance status, comorbidities, treatment with systemic and/or radiotherapy during the study period and the type and dose (converted to morphine equivalents) of the opioid which the patient will use.

The primary outcome measure is the proportion of patients with a score of < 30 on the Bowel Function Index (BFI), measured on day 14. The BFI is a clinician-administered, patient-reported questionnaire to assess clinically significant constipation, validated in patients receiving opioids for chronic non-malignant and malignant pain [20–22]. The BFI consists of three questions, assessing ease of defecation, feeling of incomplete bowel evacuation and personal judgement of the patient regarding constipation, each during the last 7 days and each rated on a scale of 0 (best possible outcome) to 100 (worst possible outcome). A total score ≥ 30 (mean of the three separate scores) indicates clinically significant constipation. A change of the total score of > 12 is regarded as clinically meaningful. The BFI has been used in a large ‘real world’ observational study in cancer patients receiving opioids [1] and in randomized trials of opioid antagonists for OIC [23–26]. It has been recommended as the assessment tool of choice for OIC [7, 27]. The BFI will be administered by the local investigator on day 0 (at the start of the study, after giving informed consent and before the randomization) and by telephone on day 14.

As a secondary outcome measure, the local investigator will assess the Rome IV criteria for opioid-induced constipation on day 0 and by telephone on day 14 (see Table 1). At least two of the six criteria have to be fulfilled in order to diagnose constipation.

Another secondary outcome measure is the 5-level EuroQol-5 Dimension questionnaire (EQ-5D-5L) completed on day 0 and 14. The EQ-5D-5L is a self-administered, generic assessment tool developed by the EuroQol Group to assess the quality of life and to determine cost-effectiveness. This measurement tool consists of five questions on dimensions of health (i.e., mobility, self-care, pain/discomfort, usual activities, and anxiety/depression) [28].

Other secondary outcome measures include a pain score (Numeric Rating Scale, ranging from 0 to 10, on days 0 and 14), a questionnaire about patient satisfaction with the laxative on day 14 (one question on a four-point Likert scale, ranging from unsatisfied to very satisfied), a questionnaire about side effects of the laxatives on day 14 and a questionnaire about medical consumption (the modified iMTA Medical Consumption Questionnaire (iMCQ)) on day 14 [29]. An overview of the measurement tools can be found in Table 1.

Lastly, patients will report daily laxative use in a medication diary to evaluate protocol adherence and also daily use of escape medication.

**Table 1 Tab1:** Overview of measurement tools

Measurement tool	
Bowel Function Index (Day 0 and day 14)	3 questions about defecation, rated on a scale of 0 (best possible outcome) to 100 (worst possible outcome). Total score ≥ 30 (mean of the three separate scores) indicates clinically significant constipation. A change of the total score of > 12 is regarded as clinically meaningful.
Rome IV criteria for opioid-induced constipation (Day 0 and day 14)	At least two of the following criteria have to be fulfilled in order to diagnose constipation: - Straining > 25% of defecations - Lumpy or hard stools in > 25% of defecations - Sensation of incomplete evacuation in > 25% of defecations - Sensation of anorectal obstruction/blockage in > 25% of defecations - Manual manoeuvres to facilitate > 25% of defecations - < 3 spontaneous defecations per week
EQ-5D-5L questionnaire (Day 0 and day 14)	5 questions on dimension of health: mobility, self-care, pain/discomfort, usual activities, and anxiety/depression. Each dimension consists of 5 levels: no problems, slight problems, moderate problems, severe problems and extreme problems
Pain (Day 0 and day 14)	Numeric rating scale (0 = no pain, 10 = worst pain imaginable) Satisfaction with laxatives will be scored on a four-point Likert scale, ranging from unsatisfied to very satisfied Side effects of laxatives (i.e. bad taste, flatulence and nausea) will be scored on a four-point Likert scale (not at all, a bit, rather, very much)
Patient satisfaction (Day 14)	
Side effects (Day 14)	
Modified iMCQ (Day 14)	9 questions related to frequent occurring contact with healthcare providers. Each answer is dichotomous (yes/no) with the option to add the number of visits if the answer ‘yes’ is filled in.

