### Sample size calculation

The sample size was determined to achieve 90% power to declare non-inferiority of magnesium hydroxide in case the proportion of patients with a score < 30 on the BFI at day 14 to be equal for magnesium hydroxide and macrogol/electrolytes assuming one-sided testing at a significance level of 2.5% [30]. The sample size was based on two non-randomized studies that showed that approximately 40% of patients starting with opioids and not using laxatives do not develop constipation after 14 days [31, 32]. Prophylaxis with laxatives can only be effective in (part of) the remaining 60% of patients. Treatment with macrogol/elektrolytes is effective in 70% of patients with symptomatic chronic constipation [33, 34]. Based on these data, we estimated the percentage of patients without constipation (BFI < 30) after 14 days of treatment with macrogol/electrolytes to be 82% (40% plus 0,7 × 60%). The main considerations are that the proportion of patients with a BFI < 30 under magnesium hydroxide at the non-inferiority margin should clearly be higher than the estimated 40% of patients without opioid induced constipation and the clinical judgement that more than 15% difference could no longer be translated in a conclusion that magnesium hydroxide is non inferior to macrogol/electrolytes. Based on the previous data, we calculated a sample size of 138 evaluable patients per arm. We will increase the inclusion with approximately 20% to anticipate potential loss to follow-up to N = 165 per arm.

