### Statistical analysis

All data will be coded and collected in a secure cloud-based clinical data management platform (Castor EDC). Analysis will be performed using the latest version of IBM SPSS Statistics.

Primary analysis for non-inferiority will be performed both on a protocol and intention-to-treat basis. The primary outcome is the difference in proportion of responders (BFI < 30 at day 14) between the two arms. The primary analysis will use the Newcombe score method to estimate a one-sided 97.5% confidence interval for the difference in proportion of responders (proportion responders under magnesium hydroxide minus proportion responder under macrogol/electrolytes). The null hypothesis (H0: Magnesium hydroxide is inferior to macrogol/electrolytes in the prevention of OIC) will be rejected and non-inferiority will be claimed for magnesium hydroxide if the lower boundary of the 97.5% confidence interval is larger than the prespecified non-inferiority margin of -15%. An additional analysis will be performed in which the risk difference for response is estimated using a generalized linear model for a binomial outcome and an identity link, while adjusting for the stratification factors of center and constipation at the start of the study.

An additional per protocol analysis will be performed using inverse-probability-of-treatment-weighing (IPTW) in the intention-to-treat population. For this IPTW analysis, logistic regression analysis in the intention-to-treat population will be used to predict the probability of a subject being adherent based on predefined confounders. In this analysis, non-adherence is defined as < 80% of the prescribed laxative being taken as determined from the patient diary [35]. The inverse of the predicted probabilities will then be used as weights in an analysis comparing treatment outcomes between the groups and to estimate a per-protocol effect. In this weighted analysis, the risk difference for response and its two sided 95% confidence interval is estimated using generalized linear models for a binomial outcome and an identity link, while adjusting for the stratification factors.

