Secondary analyses include the same analyses for constipation judged by professional care givers, based on the Rome IV criteria for opioid-induced constipation. Furthermore, we aim to study baseline predictors of the response to macrogol/electrolytes and magnesium hydroxide in patients starting with opioids, including sex, age, performance status and comorbidity.

Lastly, the cost-effectiveness of macrogol/electrolyte compared to magnesium hydroxide will also be a secondary outcome. The cost-effectiveness will primarily be influenced by the effect of the medication on healthcare resource use and quality of life, since their unit costs are similar. In this analysis, we will compare the cost-effectiveness of macrogol/electrolyte and magnesium hydroxide in patients. The analysis will be performed from a healthcare perspective with a time horizon of two weeks. A decision tree will be developed with branches for initial therapy and responders and non-responders. The costs and quality of life of the patients in the trial will be used as input for this decision tree. This requires data collection on healthcare procedures and quality of life in responders, non-responders and patients with side-effects of laxatives for the follow-up period of the study (two weeks). These healthcare procedures will be extracted from the modified iMCQ after two weeks. The modified iMCQ will be adjusted in such a way that resource use due to gastrointestinal complaints will only be measured in these patients with intensive healthcare resource use. All individual health care procedures will be linked to their unit costs. Reimbursement prices issued by the Dutch Healthcare Authority (NZa) and national reference prices will be used for this assessment as outlined in current Dutch pharmaco-economic guidance. Quality of life will be measured using the EQ-5D-5L at baseline and after two weeks.

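### The supportive adjusted models reduce the day-0 BFI score to a yes/no term, although the full score is known before randomisation for every patient; using it would bring a modest gain.

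*Protocol article*

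**What the plan says.** All references are to the protocol article.

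- **Study measurements.** "The BFI will be administered by the local investigator on day 0"; the same sentence places this after consent and before randomisation. The score is the mean of three items, each rated 0 to 100. A value of 30 or more counts as clinically significant constipation, and a change of more than 12 points counts as clinically meaningful. Baseline data also include "the type and dose (converted to morphine equivalents) of the opioid which the patient will use".
- **Randomization, blinding and treatment allocation.** "Randomization will be stratified by center and presence of constipation at the start of the study", the latter meaning a BFI of 30 or more. Randomisation follows the baseline assessments.
- **Statistical analysis.** Non-inferiority is judged on an unadjusted Newcombe interval against a margin of -15 percentage points. An additional binomial model with identity link estimates the risk difference "while adjusting for the stratification factors of center and constipation at the start of the study". The weighted per-protocol analysis uses the same type of outcome model with the same factors. Its weights come from a separate adherence model whose confounders the article does not list.
- **Statistical analysis, secondary analyses.** Baseline predictors of response will be studied, "including sex, age, performance status and comorbidity".

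**The concern.** The article fixes the covariates of both outcome models, so this is a stated choice and not a detail left open. The yes/no term treats a patient with a day-0 score of 0 and one with a score of 29 as the same. That band is more than twice the 12-point change that the article itself calls meaningful. Entry requires four weeks without laxatives and more than four weeks without opioids. Most patients will therefore probably fall below 30, where the term cannot tell them apart; this is an inference, as the article gives no baseline distribution.

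At stake is the precision of two supportive estimates of the risk difference. If the day-0 score predicts day-14 status within a stratum, their intervals will be wider than the collected data allow.

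**Working it through.** **1. Is the score available?** Yes. It is taken before randomisation, and a patient cannot be assigned to a stratum without it, so it is complete by design.

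**2. The plan's own precision.** Inputs from Sample size calculation and Statistical analysis: 82% response in both arms, margin 15 points, one-sided 2.5%, 90% power.

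- n per arm = (1.960 + 1.282)² × 2 × 0.82 × 0.18 / 0.15² = 137.9, so 138. The stated figure is reproduced and does not rely on covariate adjustment.
- At 138 per arm, SE = √(2 × 0.82 × 0.18 / 138) = 4.63 points, and the 95% half-width is 9.06 points.

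**3. Extra gain from the score.** Let R² be the share of outcome variance that the covariates explain. The further variance reduction from adding the score to the stratum is

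reduction = 1 − (1 − R² with score and stratum) / (1 − R² with stratum only).

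Assumptions, none of them in the article: bivariate-normal latent BFI, 30% of patients at the floor score of 0, and 10-30% with BFI ≥ 30 at day 0. Response is 82%, as planned. This was evaluated by simulation with 400,000 pairs per setting.

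| Day-0/day-14 correlation | Baseline BFI ≥ 30 | Further variance reduction |
|---|---|---|
| 0.5 | 10% | 6.0% |
| 0.5 | 20% | 4.5% |
| 0.5 | 30% | 4.0% |
| 0.3 to 0.6 | 10-30% | 1.3% to 9% |

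At a correlation of 0.5 the stratum alone explains 7-9% of the outcome variance, and score plus stratum 12.5-13%.

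**4. What that means for an interval.** Width scales with √(1 − reduction): √0.987 = 0.993 and √0.91 = 0.954, so intervals are about 0.7% to 4.6% narrower. Applied to the planning half-width of 9.06 points for scale, this gives 9.0 and 8.6 points; a 5% reduction gives 8.84. In patient terms, 276 × (1/(1 − 0.013) − 1) = 3.6 and 276 × (1/(1 − 0.09) − 1) = 27.3, or about 4 to 27 of the 2 × 138 = 276 evaluable patients. These equivalents describe the unweighted adjusted model only.

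**5. A second model as a check.** Assumptions: a skewed 0-100 baseline BFI with 20% or 35% at or above 30, and a logistic outcome with 82% response. Using the continuous score in place of the yes/no term lowered residual variance by about:

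- 0.5% for a slope of 0.3 log-odds per SD;
- 2.3-2.5% for a slope of 0.6;
- 6-7% for a slope of 1.0.

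The range overlaps that in step 3. The gain is positive in every setting and small at the lower end.

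**6. Can the planned model take the score?** Identity-link fits were simulated with 276 patients and 11 center terms, 60 trials per setting. With the yes/no factor, 43-83% failed to converge or gave fitted risks outside 0 to 1; with the continuous score, 72-100% did. These rates depend on software and starting values and are indicative only. They show that adding the score means changing the estimator.

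**The case against.** The strongest reply is that adjusting for the stratification factors is standard and valid, that nothing is misstated, and that the result of the trial is untouched. All of that stands. Four stronger readings may tempt a reader, and the article does not support them.

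- **The trial loses power.** It does not. The claim of non-inferiority rests on the unadjusted Newcombe interval, and the affected models are additional analyses.
- **The estimates are biased by chance imbalance.** Under randomisation, such imbalance is random error, which the confidence interval already covers.
- **Opioid type and dose are ignored.** Only the BFI is explicitly taken before randomisation. For the opioid this is inferred from its listing as baseline data, and the same list includes cancer treatment during the study period. The unlisted confounders of the adherence model may include the opioid or the day-0 BFI. The list of predictors is open-ended, so it cannot be said that the predictor analysis leaves opioids out.
- **The gain costs nothing.** Step 6 of the working shows that the identity link would have to go.

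It is also fair to say that the correlation is assumed. It links bowel function around the start of opioids, without laxatives, to function after 14 days on an opioid and a laxative. The simulated gain is for unweighted models and cannot be carried over to the weighted analysis as a number.

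What the reply does not remove is that the article fixes the outcome-model covariates, and that a score already held for every patient is cut to two categories there.

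**Conclusion.** The point holds as an optional gain in efficiency. Both supportive outcome models use day-0 BFI only as a split at 30, although the full score is collected before allocation for everyone. Replacing the split by score plus split would lower the variance of the adjusted risk difference by about 1-9%, if the day-0/day-14 correlation lies between 0.3 and 0.6 and the other assumptions above are roughly right. A weaker relation would bring less, down to 0.5% in the second model. No figure can be given for the opioid variables or for the weighted analysis. The plan as written remains valid, and its 90% power does not depend on this choice.

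**What to change.** For day-14 BFI < 30, in both the additional adjusted analysis and the outcome model of the weighted per-protocol analysis:

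1. Keep center and baseline constipation, and add the continuous day-0 BFI as a prespecified covariate.
2. Fit a logistic model and standardise it over the analysed patients to obtain the risk difference, in place of the identity-link model. Use a robust or bootstrap standard error that suits the standardisation and, where relevant, the weights.
3. Optionally add opioid type and starting dose in morphine equivalents, provided the sponsor confirms that the values used are those fixed before allocation.

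The wording should be settled before outcome data are seen, so that covariates are not chosen after the fact. The cost is a change of estimator and a little more analysis work. It needs no new data, visits or patient burden, and the primary analysis stays as it is.

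### Side effects are scored only on day 14, after the laxative may already have been reduced or stopped for intolerance, so a difference in tolerability may be understated

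*Protocol article*

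**What the plan says.** The Background of the Protocol article states that the trial "compares side-effects, tolerability and cost-effectiveness". The Discussion and Conclusion repeat the promise on tolerability and side effects.

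Study measurements lists "a questionnaire about side effects of the laxatives on day 14", and the entry in Table 1 likewise reads "Side effects (Day 14"). The same table gives day 0 and day 14 for the BFI, Rome IV, EQ-5D-5L and pain. The content is given as "Side effects of laxatives (i.e. bad taste, flatulence and nausea) will be scored on a four-point Likert scale". No recall period is stated for these items. The BFI items, by contrast, are "each during the last 7 days and each rated on a scale of 0 (best possible outcome) to 100 (worst possible outcome").

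The Treatment section says that the dose of either laxative "may be decreased or discontinued because of intolerance or side effects during the study period". To decide on dosage, "a contact moment with the local investigator by telephone will take place on day 7". No side-effect instrument is listed for that call.

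On laxative use, "patients will report daily laxative use in a medication diary to evaluate protocol adherence and also daily use of escape medication". Reduction or stopping for intolerance does not appear among the secondary outcomes in Study measurements or Statistical analysis.

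**The concern.** The patients who tell us most about tolerability are those who cut or stop the laxative because of it. They are also the patients most likely to have had the cause reduced or removed before anyone scores their symptoms. Someone who stops on day 4 because of nausea has been off the drug for ten days on day 14. If asked about present or recent symptoms, that patient can truthfully choose the lowest category. Because the dose change itself is not a listed outcome, the event that shows intolerance need not appear in the tolerability comparison either.

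The sample size assumes equal efficacy, and Statistical analysis describes the unit costs of the two drugs as similar. If non-inferiority is shown, tolerability may weigh heavily in choosing between them. That is an inference, not something the article says. The economic analysis also asks for data on patients with side effects, a group that could be undercounted.

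**Working it through.** **1. The plan's own figure.** The only related number is the primary sample size. With 82% in both arms, a margin of 15 points, one-sided 2.5% and 90% power: n = (1.960 + 1.282)² × 2 × 0.82 × 0.18 / 0.15² = 10.51 × 0.2952 / 0.0225 = 137.9, so 138 per arm, as stated. 138 × 1.20 = 165.6, consistent with the stated 165. Neither figure depends on side effects. The 138 is used below only to show power.

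**2. Model.** Let p be the true proportion with a side effect at any time in the 14 days, and s the share of those patients who have reduced or stopped, are symptom-free, and do not report the symptom on day 14. Subscript 1 is the worse-tolerated arm.

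- Observed proportion = p × (1 − s)
- Loss in the observed difference = p₁s₁ − p₂s₂

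**3. Results.** The documents give neither p nor s, so every value below is assumed. Power is two-sided 5% with 138 per arm.

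| True p₁ v p₂ | s₁ v s₂ | Observed | Difference (points) | Power |
|---|---|---|---|---|
| 40% v 25% | 0 v 0 | 40% v 25% | 15 | 76% |
| | 20% v 20% | 32% v 20% | 12 | 62% |
| | 40% v 40% | 24% v 15% | 9 | 47% |
| | 40% v 20% | 24% v 20% | 4 | 12% |
| | 60% v 20% | 16% v 20% | −4 | wrong direction |
| 30% v 20% | 0 v 0 | 30% v 20% | 10 | 48% |
| | 20% v 20% | 24% v 16% | 8 | 38% |
| | 40% v 40% | 18% v 12% | 6 | 29% |
| | 40% v 20% | 18% v 16% | 2 | 6% |
| | 60% v 20% | 12% v 16% | −4 | wrong direction |

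**4. When the difference vanishes.** This needs p₁(1 − s₁) = p₂(1 − s₂). With s₂ = 20%, s₁ must reach 1 − (20/30) × 0.8 = 47% in the second scenario, or 1 − (25/40) × 0.8 = 50% in the first. Equal shares shrink the absolute difference but leave the ratio unchanged (1.6 and 1.5).

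**5. Direction.** The difference is understated when p₁s₁ > p₂s₂, that is, with equal shares or with a larger share in the worse-tolerated arm. It could be overstated if resolution were clearly more common in the better-tolerated arm: 30% v 20% with s = 20% v 40% gives 24% v 12%, or 12 points instead of 10.

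**6. Role of the recall period.** If the day-14 items cover all 14 days and are recalled fully, s = 0 among those who answer, and nothing is lost. If they used a 7-day window like that of the BFI, the first week, before the day-7 dosage call, would be left out.

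**The case against.** The strongest objection is that day 14 is the date of asking, not the period asked about. The questionnaire is not printed, an article commonly leaves such wording to the full protocol, and whole-period recall would remove the mechanism for everyone who answers. This stands, and it is why the point is conditional. It does not help for a patient who stops for intolerance and gives no day-14 answer; the plan allows about 20% for loss to follow-up.

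One might also read the two-week follow-up period named in the economic part of Statistical analysis as showing that the side-effect items span both weeks. That phrase describes the collection of healthcare use and quality of life, so it does not settle the matter.

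The diary does show stopping, so the event is not invisible. But its stated use is adherence and escape medication, it is described as recording use and not reasons, and adherence is measured against the prescribed amount, so an agreed reduction may not register.

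A day-14 score under permitted dose changes is a valid comparison of the symptoms that remain after adjustment. That is a narrower question than tolerability.

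Finally, the Discussion deliberately confines questionnaires to the start and end to spare palliative patients. That is a fair reason for restraint, but the day-7 call already takes place to review dosage, so three items add little.

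A reader might infer that the comparison is biased outright, or that a true 10-point difference would disappear (30% v 20% becoming 10% v 10%). The documents do not support this. That example needs 67% v 50% of affected patients to resolve and report nothing, and no rate in the article supports those shares.

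**Conclusion.** The point holds as a risk, not as a demonstrated bias. Side effects are scored once, after dose reduction and stopping for intolerance have been allowed, with no stated recall period and no listed outcome that counts those changes. Unless the questionnaire covers the whole 14 days, a difference in tolerability may be understated, to the advantage of the worse-tolerated drug.

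The size cannot be stated from the documents. With equal resolution shares of 20% to 40%, a difference of 15 points becomes 12 to 9, and one of 10 becomes 8 to 6. Near-disappearance or reversal requires much more resolution in the worse-tolerated arm. All of this assumes that resolved symptoms go unreported. The primary outcome and the sample size are unaffected. The change is worth making because it is cheap and serves a stated aim.

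**What to change.** - Score bad taste, flatulence and nausea, on the same four-point scale, at the existing day-7 call and before any dose change is agreed.
- Word the day-14 items as worst severity since day 0, and analyse each patient's maximum of the two scores by arm.
- Record the reason for any dose reduction or stop.
- List the proportion with reduction or discontinuation for intolerance by day 14 as a tolerability outcome, and compare it between arms in all randomised patients.

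The cost is a few questions at a call that already takes place, a changed recall phrase, one added field for the reason, and one table. The extra questions should be weighed against the burden aim in the Discussion. Recruitment began in October 2022 (Study design), so day-7 scores and the new wording can cover only patients enrolled from the change onwards, and the report should say how many that is. No dosing rule changes.
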